#### Specific aim #2:

The length of the procedure, technical aspects of the procedure and perioperative complications will be recorded. Analysis of this data will allow estimation of the types of adverse events (AEs), operative complication rate and median length of surgery.

#### Specific aims #3 and #4:

Patient satisfaction with VMMC will be assessed at every postoperative visit. Forms 6 and 7 ask clients about their satisfaction or dissatisfaction with the procedure and their partners acceptability of their VMMC. Subjects will also be asked if they have recommended VMMC to other men. If so, we will record and estimate the most common reason for recommending the procedure to their peers. Other outcomes to be recorded and analyzed include: number of men requesting VMMC by age; number circumcised by age and marital status; proportion circumcised who are HIV tested and counseled; time and personnel involved in each surgery; proportion of circumcisions with moderate and severe AEs by day of ascertainment, and proportion of men who resume sex before 42 days post-surgery.

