An aliquot of the patient's serum (2 mls) will be preserved for future testing at the University of Illinois. As long as the investigators hold personal identifiable information, participants will be informed of the results of any future testing performed on their blood and will be offered treatment free of charge and referrals as outlined above. Section d.3 provides a complete description of how these samples will be managed, preserved and transported. Urine will not be preserved for future testing.

If there is a temporary, medically curable condition present, such that it would be advisable to defer potential surgery, then the participant will be treated and asked to return for re-evaluation for study eligibility when he is cured. Men found to have an STD or to be HIV-positive will be referred for immediate care. Once enrollment is completed, participants will be given an appointment for the surgery.

Circumcision will be performed soon after informed consent, preferably within a few days. All surgeries will be done under local anesthesia in a clinic by trained clinicians, using the standardized forceps-guided method described by Krieger and colleagues and contained in the WHO MC manual. Circumcised men will be counseled to refrain from sex for six weeks post-surgery and counseled about risk of HIV infection through open wounds during the healing process. They will be checked for complications and asked about their sexual activity seven days after the procedure. Men without complications will be followed six months after surgery with behavioral risk assessment, HIV testing and counseling. Men may come to the study sites for unscheduled visits at any time during the 6 month follow-up. All men will be counseled at enrollment and all follow-up visits to reduce their risk for HIV infection by consistent condom use and, where applicable, reductions in numbers of sex partners. Counselling on condom use and sexual risk reduction will be provided by trained, experienced, native-speaking counsellors.

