#### *Day 7 Post Circumcision Visit (form #5)*

Circumcised men will be asked to return to the clinic 7 days after the procedure to check the wound, to see if it is healing properly, to check for complications, and to ask about their sexual activity, their level of pain, resumption of work or other activities, and their satisfaction with the procedure and care at the clinic. As with all visits, any adverse events will be recorded. Blood and urine will be collected for STD testing at this visit.

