### Outcomes

The primary objectives of the proposed study are to assess the uptake, safety (adverse event rate) and patient satisfaction, train providers and build capacity on VMMC in the Dominican Republic. In addition, we will assess risk behaviors before and after VMMC and build key partnerships with the MoH of the DR and other stakeholders, which will

help develop a proposal to the NIMH to conduct operational research in the context of larger scale provision of MC services.

The study will assess the number of patients who undergo the procedure and the degree of post-operative satisfaction.

We will also record immediate complications of the circumcision procedure, which include: 1) pain, 2) excessive bleeding, 3) anesthetic-related complications, 4) excessive skin removal and 5) damage to the penis. Early post-surgical complications will include the occurrence of any of the following within one month of the procedure: 1) pain, 2) excessive bleeding, 3) excessive skin removed, 4) insufficient skin removed, 5) swelling or hematoma, 6) damage to the penis, 7) infection, 8) delayed wound healing, 9) problem with the appearance of the penis, and 10) problems with voiding.

The following complications will be evaluated at six months after the procedure: 1) infection, 2) delayed wound healing, 3) problem with the appearance of the penis, 4) excessive skin removed, 5) insufficient skin removed, 6) torsion of the penis, 7) erectile function problems, and 8) psycho-behavioral problems. In addition to the 8-day and six month post-surgery visits, men will be encouraged to come to the clinic for an unscheduled visit at any time they have excessive pain, they have bleeding, they detect an infection, or they desire treatment for any reason. Complications will be recorded at those unscheduled visits as well. See the sections on Adverse Events and Reporting Adverse Events below for more detail.

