### Adverse Events

The presence or absence of adverse events will be recorded at every visit. So as not to miss any event that could be considered adverse, we will apply a broad definition adapted from the definition and recorded in the ICH Guideline for Good Clinical Practice:

*An adverse event is any untoward medical occurrence in a participant and that does not necessarily have a causal relationship with the treatment. An adverse event can therefore be any unfavorable and unintended sign (including an abnormal laboratory finding), symptom, or disease temporarily associated with the beginning of the treatment (i.e., following randomization).*

Adverse events will be characterized as mild, moderate, severe or death, and not related, possibly related, probably related or definitely related to the circumcision procedure.

The following table lists adverse events that are related to the intervention (circumcision procedure), according to the time that they will be ascertained, and provides definitions of severity. If death occurs as a consequence of an adverse event, this will be noted and recorded as well.

| Adverse Event Type | Description of Adverse Event Type                                                                | Severity |
|---------------------------|---------------------------------------------------------------------------------------------------------|-----------------|
|                           |                                                                                                         |                 |
| A. During Surgery  |                                                                                                         |                 |
| Pain                      | 3 or 4 on pain scale                                                                                    | Mild            |
|                           | 5 or 6 on pain scale                                                                                    | Moderate        |
|                           | 7 on pain scale                                                                                         | Severe          |
| Excessive bleeding        | More bleeding than usual, but easily controlled                                                         | Mild            |

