|                                          | Additional non-operative treatment required                                                        | Moderate |
|                                          | Requires re-operation to correct                                                                   | Severe   |
| Appearance                               | Client concerned, but no discernable abnormality                                                   | Mild     |
|                                          | Significant wound disruption or scarring, but does not require re-operation                        | Moderate |
|                                          | Requires re-operation to correct                                                                   | Severe   |
| Problems with voiding                    | Transient complaint that resolves without treatment                                                | Mild     |
|                                          | Requires a special return to the clinic, but no additional treatment required                      | Moderate |
|                                          | Requires referral to another facility for management                                               | Severe   |
|                                          |                                                                                                    |          |
| C. One Month or More Post-Surgery |                                                                                                    |          |
| Infection                                | Erythema more than one cm beyond incision line and purulence in 2 or less suture points            | Mild     |
|                                          | Purulent discharge from the wound in more than 2 suture points                                     | Moderate |
|                                          | Cellulitis or wound necrosis                                                                       | Severe   |
| Delayed wound healing                    | Healing takes longer than usual, but no extra treatment necessary                                  | Mild     |
|                                          | Additional non-operative treatment required                                                        | Moderate |

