#### Reporting Adverse Events

As indicated above, the attending physician (co-investigator) will determine whether an adverse event is serious. The physician performing the MC or examining the patient during a follow up visit, will inform the on-site co-investigator, in person, of the occurrence of an adverse event or death. This communication will occur verbally and in

person since these individuals will be working within the same clinic, several feet from each other. All deaths and AEs categorized as serious will then be reported to the P.I. promptly via e-mail by the Study co-investigator within two days of the event. The study co-investigator will complete and adverse event form and will fax to the P.I. shortly after the occurrence. The P.I. will then report the AE to the UIC and Dominican IRB within 48 hours. The relationship of the AE will be specified as definitely, probably, possibly or not related to study procedures. The occurrence and type of AE, its severity, and its relationship to the circumcision procedure will be determined by the project local co-investigator in consultation with the surgeon and the principal investigator. A summary of how the severity and relationship was determined will be provided to the P.I. In case of any question, the P.I. will speak with the project staff by telephone for clarification.

AEs will be delineated by type, number of days from surgery (day of surgery being Day 0), level of severity (mild, moderate, severe, death) and relationship to the study procedures. AEs will also be listed by date and type to detect any patterns in timing of AE. For example, if a cluster of infections is detected, a review of infection control procedures may be warranted.

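### Early complications are defined by when they occur but graded and tabulated by when they are found, so one first reported at month 6 may have no grading row or a lower grade

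*Protocol*

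**What the plan says.** Four places in the protocol deal with the timing of complications.

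- **Outcomes** uses occurrence: "Early post-surgical complications will include the occurrence of any of the following within one month of the procedure". Ten types follow. A separate list of eight is to be evaluated at six months.
- **Adverse Events** introduces the grading table as listing procedure-related events "according to the time that they will be ascertained". Section A covers surgery. Section B covers post-surgical complications and gives no time limit in its heading. The last section is headed "C. One Month or More Post-Surgery".
- **d.2, Specific aims #3 and #4** plans the "proportion of circumcisions with moderate and severe AEs by day of ascertainment".
- **Reporting Adverse Events** describes each event by days from surgery, with surgery as Day 0, and adds: "AEs will also be listed by date and type to detect any patterns in timing of AE". It does not say whether the count runs to onset or to report.

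On visits, men are "asked to return to the clinic 7 days after the procedure", and "Men without complications will be followed six months after surgery". Unscheduled visits are encouraged, but the participant has to initiate them.

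The general adverse event definition places events as "temporarily associated with the beginning of the treatment (i.e., following randomization", although the study has a single group and randomizes no one.

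**The concern.** Two time bases are in use, and nothing says which prevails when they disagree. They can disagree because no visit is scheduled between day 7 and month 6. Taking one month as 30 days, days 8 to 30 are 23 of the 30 days in the early window.

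Safety is one of the study's primary objectives, so it should be clear where a late-reported early event is counted and how it is graded. A rule based on ascertainment can send it to a part of the table that was not written for it. The check for clusters of events in time also works only if the listed dates are close to onset. An analysis plan written later cannot recover onset dates that were never collected.

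**Working it through.** The protocol gives no figure to reproduce on this point. The check compares the table sections row by row and then shows the scale.

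**1. Rows in B and C**

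| | Types | Count |
|---|---|---|
| In B and C | excessive skin removed, insufficient skin removed, infection, delayed healing, appearance | 5 |
| In B only | pain, bleeding, swelling/hematoma, damage to the penis, wound dehiscence, voiding problems | 6 |
| In C only | torsion, erectile dysfunction, psycho-behavioral problems | 3 |

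B has 5 + 6 = 11 types and C has 5 + 3 = 8. The eight in C match the six-month list under Outcomes. Dehiscence is in B but not among the ten early types under Outcomes, so the conflict with that definition covers five of the six B-only types.

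**2. A worked case.** A hematoma on day 12 with significant tenderness is first mentioned at month 6. Under Outcomes it is early. By time of ascertainment it belongs to C, which has no hematoma row. The general mild/moderate/severe scale after the table is introduced for events that are not, or may not be, related to the procedure. It does not clearly cover an obvious surgical complication.

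**3. A change of grade.** In B, purulent discharge is moderate. In C, erythema with purulence in two or fewer suture points is mild, and purulent discharge becomes moderate only above two. An early infection graded under C can therefore leave the moderate/severe numerator.

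**4. How many could slip through.** The six B-only types have 6 × 2 = 12 moderate or severe grades. Eight are defined by care given: both grades of bleeding, dehiscence and voiding problems, severe hematoma, and moderate damage. These would normally be ascertained at the time of treatment. Of the other four, severe damage could hardly go unnoticed. That leaves moderate pain, severe pain and moderate hematoma.

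**5. Scale.** Inputs are the planned 500 subjects and hypothesis H2 (complication rate below 2%). Assumptions: all 500 are circumcised, and H2 is judged on moderate and severe events, which the protocol does not state. The rate is k/500. The Clopper-Pearson 95% limits are the 0.025 quantile of Beta(k, 500 − k + 1) and the 0.975 quantile of Beta(k + 1, 500 − k).

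| Events counted (k) | Rate | 95% CI |
|---|---|---|
| 10 | 10/500 = 2.0% | 0.96% to 3.65% |
| 9 | 9/500 = 1.8% | 0.83% to 3.39% |
| 8 | 8/500 = 1.6% | 0.69% to 3.13% |

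Each event lost lowers the rate by 1/500 = 0.2 percentage points.

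**The case against.** The best defense is that the protocol is mixed in its wording and does not apply ascertainment throughout. The sentence introducing the table may only describe its layout. Section B has no stated time limit, so a hematoma recalled at month 6 could be graded there. Days from surgery may already mean days to onset, and the adverse event form, which is not in the document, may already have an onset field. Serious events are to be reported within two days of the event, which presupposes an event date. Tabulating by day of ascertainment is legitimate when labeled as such, and no hypothesis compares early with late complications.

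Most of this stands, and it limits the point to an unresolved inconsistency. It does not remove it: the heading of C and the stated basis of the table still direct a month-6 report to C, and nothing says otherwise.

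Three stronger readings are tempting, and the document does not support them.

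- **That the overall complication rate is biased by misplaced events.** Moving an event between periods leaves the total unchanged. Only an event left ungraded or downgraded can alter it, and a downgraded one only if mild events are excluded.
- **That events found at day 7 are put in the wrong period.** A bleed on day 2 recorded at day 7 is still early. Only the by-day profile shifts.
- **That a percentage of misplaced events can be given.** This needs a distribution of onset times and a rate of unscheduled visits. The protocol gives neither.

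**Conclusion.** The point holds as an inconsistency to be reconciled. An early complication first reported at month 6 is early by the outcome definition but, read literally, is graded in section C. There, six of the 11 post-surgical types have no row, and an infection with limited purulence can fall from moderate to mild.

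The number of such events is unknown and probably small, mainly moderate or severe pain, moderate hematoma and limited infection. The effect on the moderate/severe rate is 0.2 percentage points per lost event under the assumptions above. That matters for H2 only if the observed rate lies close to 2%.

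The mention of randomization is leftover wording. A reader might infer that the adverse event window has no start, but the same sentence refers to the beginning of treatment and section A of the table begins at surgery.

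**What to change.** Reconcile Outcomes, Adverse Events, Reporting Adverse Events and d.2 on one basis:

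- Assign each complication to a period and a grading section by day of onset from surgery (Day 0), whatever the day it was reported.
- Give section B an explicit time limit consistent with Outcomes.
- State that days from surgery run to onset.
- Confirm that the adverse event form records the onset date, or the best recalled day, and add the field if it does not.
- Keep the ascertainment date as a second column, so that the tabulation planned in d.2 can still be produced.
- In the adverse event definition, replace the reference to randomization with the start of the circumcision procedure.

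The cost is some rewording and at most one date field. The small downside is that onset dates recalled at month 6 will be approximate and should be flagged as such.

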#### Specific aim #5:

Specific questions on sexual practices, time of resumption of sexual activity, sexual pleasure after VMMC and partner's sexual satisfaction will be asked at follow up visits. This will allow the estimation of the proportion of men who resume sex earlier than recommended and the effects of VMMC on sexual pleasure. Behavioral disinhibition will be estimated by analyzing the subject's self perceived level of protection against HIV/STI and their risk taking behavior (i.e. low rates of condom use).

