### **a) Specific Aims:**

Based on the results of numerous observational studies and the three RCTs the World Health Organization (WHO) and the Joint United Nations Programme on HIV/AIDS (UNAIDS) have endorsed VMMC as a biomedical intervention for HIV prevention. As such, countries with a high prevalence of HIV in the population are encouraged to examine the feasibility of offering MC services as part of the portfolio of HIV prevention strategies at a national level. The specific aims for this project are:

- 1) To develop culturally appropriate education materials about the benefits of VMMC for clients attending pilot healthcare centers.
- 2) To train a core group of providers on proper surgical and counseling techniques to provide comprehensive VMMC services.
- 3) To determine the acceptability, uptake and demand for MC services in key areas of high HIV prevalence.  
H1: The acceptability and uptake among high risk men will be around 60%.
- 4) To assess the safety and adverse events of performing circumcision in resource constrained settings.  
H2: VMMC will result in a complication rate of less than 2%.
- 5) To assess sexual risk behaviors, perceptions of sexual function and sexual pleasure in men before and after VMMC. H3: there will be no differences in risk behaviors, sexual function and pleasure after VMMC
- 6) Estimate point prevalence of most common STI in a subset of circumcised men and preserve a small sample of blood to test future scientific hypothesis and/or newer testing techniques as they become available.
- 7) To build collaborations with the MoH and other partners in the DR and at UIC to develop a proposal to NIMH for operational research in the context of larger scale MC service provision.

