*Sexual behavior* will be another important outcome, particularly as there is concern that men who are circumcised may mistakenly feel that they are protected from HIV and may adopt more risky sexual behavior. On the other hand, sexual activity among circumcised men is likely to be much less for a period of time following the circumcision, which will decrease risk during that period. Self-reported sexual behavior (e.g. number of sex partners, lifetime, last 12 months and last 6 months; sex for gifts or money; condom use) will be assessed at baseline and at 6 months with a standard set of questions. We will also ask participants directly about their perceptions of change in risk for HIV acquisition.

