|                            | Requires re-operation or transfer to another facility to correct the problem                                         | Severe   |
| Erectile dysfunction       | Client reports occasional inability to have an erection                                                              | Mild     |
|                            | Client reports frequent inability to have an erection                                                                | Moderate |
|                            | Client reports complete or near complete inability to have erections                                                 | Severe   |
| Psycho-behavioral problems | Client reports mild dissatisfaction with the circumcision, but no significant psycho-behavioural consequences        | Mild     |
|                            | Client reports significant dissatisfaction with the circumcision, but no significant psycho-behavioural consequences | Moderate |
|                            | Significant depression or other psychological problems attributed by the client to the circumcision                  | Severe   |

Appropriate medical care for adverse events will be provided to all study participants, as well as surgical care if required. If referral for medical or surgical complications are required, they will be made to the referral hospitals.

As indicated above, adverse events that are not or may not be related to the circumcision procedure will also be recorded. These will generally be ascertained by the project medical or clinical officer during a scheduled or unscheduled visit, either by history or physical examination. Severity will be judged as follows:

*Mild:* Transient or minimal symptoms; did not appreciably affect activity.

*Moderate:* Notable symptoms requiring modification of activity, but not resulting in loss of work or cancellation of social activities.

*Severe:* Incapacitating symptoms, requiring bed rest and/or resulting in loss of work or cancellation of social activities, and/or significant intervention therapy, including hospitalization.

All severe adverse events will be considered serious adverse events (SAEs) for reporting purposes (see below). This is consistent with the following FDA definition of serious adverse events:

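### Aim 5 and H3 need sexual function and pleasure before and after VMMC, but the protocol describes a baseline only for risk behaviour, so two of H3's three parts cannot be tested as change and earlier erectile problems may be misattributed.

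*Protocol*

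**What the plan says.** **Aim and hypothesis.** Specific aim 5 (Protocol, section a) is "To assess sexual risk behaviors, perceptions of sexual function and sexual pleasure in men before and after VMMC". H3 states that "there will be no differences in risk behaviors, sexual function and pleasure after VMMC". H3 therefore has three parts: risk behaviour, function and pleasure.

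**Timing of measurement.** Under Outcomes, self-reported sexual behaviour (partners, sex for gifts or money, condom use) "will be assessed at baseline and at 6 months with a standard set of questions". In section d.2, Specific aim #5, questions on "sexual pleasure after VMMC and partner's sexual satisfaction will be asked at follow up visits", and the protocol says that the answers will allow estimation of "the effects of VMMC on sexual pleasure". The section on the six-month visit adds perceptions of sexual performance after the operation, as a topic of the qualitative interview.

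**Baseline forms.** Form 2 is a demographic and behavioural questionnaire completed after consent. Form 3 is the medical history and physical examination before surgery. The items on neither form are shown.

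**Erectile events.** Erectile function problems are among the eight complications evaluated at six months (Outcomes). In the Adverse Events table the moderate grade is "Client reports frequent inability to have an erection"; the mild and severe grades are worded in the same way, by how often or how completely it happens. The sentence that introduces the table begins "The following table lists adverse events that are related to the intervention (circumcision procedure". The same section also requires every event to be rated from not related to definitely related, and the not-related category is for events clearly due to another cause. The on-site co-investigator makes that judgement, in consultation with the surgeon and the principal investigator (Reporting Adverse Events).

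**The concern.** A before-and-after effect needs a value from before. If function and pleasure are asked only after surgery, the study can report how men feel at six months, or how they think they have changed, but not how they changed. Recalled change over six months in men who chose the operation is open to recall and social-desirability bias. The protocol recognises the second problem in its interview methods.

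The gap matters for the pilot's purpose. In the team's earlier acceptability survey (Preliminary studies), not believing that circumcision lowers sexual pleasure was among the strongest predictors of willingness before the information session (OR 2.18, 95% CI 1.20-3.94). A sound estimate of change in pleasure is something that the planned larger programme would want to use.

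The same missing baseline affects safety. A man who had erectile difficulty before surgery and reports it at six months meets the grade as worded. The assessor is then asked whether another cause clearly explains it, with no specified record of his earlier state. H2 sets a low limit, so a few wrong attributions could change its answer.

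**Working it through.** **1. Each part of H3 against the stated timing of its measurement**

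| Part of H3 | Stated before surgery | Stated after surgery | Testable as within-man change, as written |
|---|---|---|---|
| Risk behaviour | Yes (Outcomes) | Six months (Outcomes) | Yes |
| Sexual pleasure | Not stated | Follow-up visits (d.2, aim #5) | No |
| Sexual function | Not stated | Six-month interview on performance; erectile item in the AE table | No |

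The two scheduled follow-up visits are at day 7 and six months. Men are counselled to abstain for six weeks, so only the six-month visit can be expected to give a usable answer on pleasure. The promised effect on pleasure therefore rests on one post-operative measurement.

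**2. Relatedness of erectile events**

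The table's introduction treats its contents as related to the procedure. The sentence before it, and the definitions after the table, have relatedness rated event by event. These do not agree. The rating scale also leans one way when history is missing: not related needs a clear other cause, while the definition of possibly related takes in events for which another cause is equally or more likely. An earlier problem that nobody recorded falls more naturally into the second category.

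**3. How sensitive H2 is to such errors**

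Inputs from the Protocol:
- Sample: 500. It reproduces as 5 per week × 2 sites × 50 weeks = 500. The 50 weeks are an assumption; 52 weeks give 520.
- H2 limit: 2%, and 0.02 × 500 = 10 men.
- Parent-trial rate of procedure-related events: 1.5%, and 0.015 × 500 = 7.5 men. The margin is 10 − 7.5 = 2.5 men.

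Assumption: let b be the share of men with an earlier erectile problem that is reported at six months and wrongly counted as a complication. The documents give no value for b, and it could be close to zero. With b independent of procedural events and all 500 men circumcised and assessed:

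p = 1 − (1 − 0.015)(1 − b)

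The chance of observing 2% or more is P(X ≥ 10), with X binomial (500, p).

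| b | Men misattributed | p | Expected events | P(observed ≥ 2%) |
|---|---|---|---|---|
| 0 | 0 | 1.50% | 7.5 | 0.22 |
| 0.25% | 1.25 | 1.75% | 8.7 | 0.38 |
| 0.5% | 2.5 | 1.99% | 10.0 | 0.54 |
| 1% | 5 | 2.49% | 12.4 | 0.80 |
| 2% | 10 | 3.47% | 17.4 | 0.98 |

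The expected rate reaches exactly 2% at b = 1 − 0.98/0.985 = 0.51%, which is about 2.5 men in 500.

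**The case against.** Much can be said for the plan, and it limits the point.

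- A reader might infer that H3 as a whole is untestable. It is not: risk behaviour is asked at both times with the same questions.
- A reader might infer that function and pleasure are definitely not collected before surgery. The documents do not show that. Form 2 could hold such items, and form 3's history could touch on function. The aim #5 sentence on follow-up also lists sexual practices, which are known to be asked at baseline as well, so it is not a full account of timing. What stands is that no section states a baseline item for function or pleasure, although the protocol does state one for behaviour.
- A reader might infer that earlier erectile problems are automatically counted as related. They are not. Every event gets a relatedness rating, and not related is available. The risk is misattribution, and its size is unknown. Events are also listed by type, timing, severity and relationship, so erectile events would remain visible.
- A reader might object that H3 claims no difference without a margin. A margin is commonly left to an SAP, which is not at hand, so it is no part of this point.
- Function and pleasure are not named among the primary objectives under Outcomes, and this is a single-arm pilot with a convenience sample. That lowers the stakes, but aim 5 and H3 remain stated commitments.

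Leaving the matter to the SAP is not an answer. An analysis plan can choose a method, but it cannot supply a pre-surgical answer that was never asked for.

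**Conclusion.** The point holds in a limited form. As the protocol is written, two of H3's three parts, function and pleasure, have no described baseline and cannot be tested as within-man change. The claim that follow-up questions will give the effect of VMMC on pleasure is not supported. The risk-behaviour part is unaffected. This rests on the protocol text; if forms 2 or 3 already carry matching items, the defect is one of description only.

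The erectile grades make no reference to the pre-operative state, and the table's introduction conflicts with the event-by-event ratings, so earlier problems may be misattributed. The calculation shows how little error H2 tolerates: about 2.5 men in 500, if the procedural rate is 1.5%. It does not show that the complication rate will be inflated, because the documents give neither the frequency of earlier erectile problems nor the share that would be misjudged.

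It should be settled before the first operation, because the missing value cannot be recovered afterwards.

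**What to change.** 1. State that the same sexual function and pleasure items, with the same wording and recall period, are asked before surgery on form 2 and at six months on form 6. If the forms already contain them, say so in the Outcomes section and in d.2, Specific aim #5.
2. Analyse both as within-man change with a 95% CI. Report any directly asked perception of change separately and label it as such.
3. Keep recording every erectile event, in line with the protocol's deliberately broad adverse-event definition. Use the baseline answer when rating relatedness, so that only new or worsened problems count toward the H2 complication rate.
4. Reconcile the introduction to the Adverse Events table with the relatedness ratings, for example by describing the table as events to be looked for and graded, with relatedness rated separately.

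The cost is a few added items on an existing form, a few minutes per man, and short edits to the Outcomes, Adverse Events and d.2 text. No extra visit or participant is needed.
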